**Method:**

The Schizophrenia, Nutrition and Choices in Kilojoules (SNaCK) study is a 12-week, three-arm, cross-over, randomised controlled trial. Eighteen participants aged 18–64 years diagnosed with schizophrenia or schizoaffective disorder will be recruited from community mental health services in Australia. Participants will be randomised to receive pre-prepared meals, meal kits or a supermarket voucher as a control, crossing-over at the end of weeks 4 and 8, so that all participants experience all three study arms. Primary outcomes include feasibility (recruitment rate and retention, number of days participants use pre-prepared meals or meal kits, adherence to meals as prescribed, difficulty in meal preparation and meal wastage) and acceptability (meal provision preference ranking and implementation) of the nutrition interventions. Secondary outcomes include the effects of the intervention on metabolic syndrome components, dietary intake, quality of life and food security measures.

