## Method

### Study design

The SNaCK study is a 12-week, three-arm, cross-over, three-arm randomised controlled trial (RCT) (4 weeks per study arm) using a mixed-methods evaluation to test the feasibility, acceptability and preliminary efficacy of two dietary interventions compared with an active control condition among people with schizophrenia or schizoaffective disorder (Fig. 1). This trial was registered with the Australian and New Zealand Clinical Trials Registry (trial ID: ACTRN12623001024639) and reported according to the SPIRIT-Outcomes 2022 checklist.^
12,13
^

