### Setting and study population

Eighteen eligible participants, aged 18–64 years, will be recruited through public community mental health rehabilitation settings (Community Care Units) at Metro South Hospital and Health Services, Australia. Participants will complete all three study arms, per recommendations for participatory design and user testing activities.^
14
^

Consumers will be invited to participate in the study if they have a diagnosis of schizophrenia or schizoaffective disorder (DSM-5) and body mass index (BMI) ≥25 kg/m^2 15
^ at baseline, have had <5% body weight increase or loss in the previous 3 months and live in independent accommodation with access to a kitchen with relevant utensils and equipment. All participants must have capacity to consent, be able to follow the study instructions and procedures, and provide their informed consent.

Capacity will be determined by collaboration between the treating team and delegated research staff, in compliance with the National Health and Medical Research Council (NHMRC) National Statement on Ethical Conduct in Human Research.^
16
^ All research staff are experienced in assessing the capacity of people with severe mental illness to provide informed consent. Ability to provide informed consent will be overseen by the participant’s treating psychiatrist.

Consumers will be excluded from the study if they are experiencing acute psychiatric symptoms requiring immediate hospital admission, have obesity induced by another endocrinologic disorder (e.g. Cushing syndrome, untreated hypothyroidism), have had previous surgical treatment of obesity, have a current or prior history with risk of relapse of a severe eating disorder, have dietary allergies that preclude safe consumption of provided meals or foods, or are living with someone who prepares meals for them.

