### Intervention procedures

The two dietary interventions will be: (a) pre-prepared meals (i.e. Lite n’ Easy) and (b) meal kits (i.e. EveryPlate box with meal ingredients and preparation and/or cooking instructions). These two interventions were chosen on the basis of a review of options for pre-prepared meals and meal kits available at the time in Australia, conducted by a dietitian, which was further discussed with the research team.

All participants will receive 15 min in-person general nutrition and food safety education by a nutritionist at baseline, including hard copy resources on how to safely store and prepare food, how to identify and follow ‘best before’ and ‘use by’ dates, and information on healthy meal options aligned with the Australian Dietary Guidelines (2013).^
17
^

The order of the three arms that each participant will receive will be determined using a computer-generated randomisation table by an independent biostatistician. The data analyst will be blinded to randomisation to avoid bias, but the rest of the research team will be unblinded. This will allow the research team to ensure the timing of the ordering (dietary interventions) is aligned with the participant randomisation arm.

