#### Meal kits

EveryPlate is a commercial company in Australia. EveryPlate was selected as it provided the simplest recipes (four-step recipes) using affordable, known ingredients with the least requirements for existing pantry items or complex equipment compared with other providers. Although not currently eligible as an NDIS-subsidised meal option, meal kits were chosen as they remove the complex steps of meal planning and grocery shopping while also supporting the development of basic cooking skills with step-by-step guides, making cooking with fresh ingredients a more viable option.

For each dietary intervention phase, participants will receive one meal daily, delivered weekly, for 4 weeks. A similar amount of kilojoules (kJ) will be provided per week by the meals, with Lite n’ Easy and EveryPlate meals approximately matched for kJ content (between 2600 and 2900 kJ per meal). Meal ordering will be conducted by a nutritionist and based on nutritional quality, ease of preparation (meal kits) and participant food preference. Participant food preferences, such as a preference for major protein sources (meat, poultry, seafood or vegetarian), cuisines and spices, will be collected at baseline, and participants will be encouraged to inform the research team if their food preferences change or are not appropriately reflected in the meal selection.

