#### Efficacy

Secondary outcome measures (i.e. exploration of the preliminary efficacy of two dietary interventions) will be assessed at the start (baseline) and at the end of each 4-week block, except for dietary intake, which will be assessed at baseline and week 3 of each arm (a time frame chosen to reduce participant burden in week 4). Exploratory efficacy will be evaluated using the following measures.

Physical health measures: weight will be recorded to the nearest 0.1 kg with calibrated Ade M322600 portable scales, with the same pair of scales used throughout the trial. Height, without shoes, will be measured using a tape measure mounted on the wall, with an accuracy of 0.1 cm. BMI will be calculated as weight (kg)/height (m^2^). Waist circumference will be measured halfway between the lower border of the ribs and the iliac crest in a horizontal plane. Hip circumference will be measured around the widest portion of the buttocks in a horizontal plane. Both measures will be to the nearest 0.5 cm using a non-stretchable measuring tape. Participants will be asked to remove belts or garments that may change the shape of their bodies. Where possible, the same research staff will take measurements for a participant at baseline and follow-up time points for consistency. Waist-to-hip ratio will be calculated as waist circumference (cm) divided by hip circumference (cm). Systolic and diastolic blood pressure will be measured manually at all visits using an EliteCare Traditional Sphygmomanometer (accuracy: 0.5 mm Hg) on the left arm while sitting. Participants will be asked to avoid caffeine, smoking and physical activity for 30 min before the measurements. Pulse will be recorded after 5 min of seated rest.

24-h multi-pass dietary recall: a five-phase face-to-face assessment of dietary intake conducted by a nutritionist or dietitian. The participant is guided to iteratively provide detail about each food and drink consumed within the previous 24-h period (modelled on the US Department of Agriculture’s Automated Multi-Pass Method.^
27
^). The 24-h recall will be entered into FoodWorks Online Professional (version 2, Xyris, Brisbane, Australia) for nutritional analysis including energy, macronutrient, sodium, and core and discretionary food group intake.

Short Form 36 Health Survey: a self-rated survey, validated for people with schizophrenia,^
28

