### Data analyses

Basic tabular descriptive statistics will include sample size for each group, range of scores, means, standard deviations and coefficient of variations for continuous variables with reasonably symmetrical distributions, or median and interquartile range for highly skewed variables. Differences in baseline mean symptom severity (measured with the Positive and Negative Symptom Scale and Global Assessment of Function) will be assessed across the three groups using unstandardised mean differences.

Primary outcome measures will be assessed against predetermined criteria for feasibility and acceptability as listed in Table 2. Primary and secondary outcomes will be assessed using *t*-tests and Mann–Whitney *U*-test for continuous variables. Categorical variables will be assessed using chi-squared tests by comparing the baseline scores for all participants randomised to one arm with end-point scores (at week 4) of all participants for that arm and in the same way for the other two study arms. This within-intervention analysis will then be extended to compare the same outcomes across the three arms using analysis of variance. Potential confounders such as gender, age, physical comorbidities and BMI will be considered.

**Table 2 tbl2:** Primary outcome measures and criteria for success

Feasibility	Intervention	Data	Collection method	Success criteria
Meal adherence	Pre-prepared meals	Proportion of pre-prepared meal eaten.	Checklist	Half or more of the meal was eaten ≥80% of the days.
	Meal kit	Did you follow the recipe? Did you split the recipe into two servings? Did you eat the prescribed portion of the meal kit meal today?	Checklist	Recipe followed at least 50% of time (six of 12 recipes). Of recipes attempted, food split into two meal servings 100% of time. Half or more of the meal serving was eaten ≥80% of the days.
	Control	Proportion of voucher spent on food?	Checklist	3 of 4 weeks ‘all’ voucher spent on food.
Meal wastage	Pre-prepared meals	If prepared meals were uneaten,– what happened to leftovers?	Checklist	Of meals prepared, some or all food ‘went in bin/remained uneaten’ <25% of the time.
	Meal kit	If recipe not followed what happened to unused ingredients?	Checklist	For each kit, unused ingredients went in the bin or remained uneaten ≤1 time.
		If unused ingredients at end of week, what happened to them?	Checklist	For each kit, unused ingredients went in the bin or remained uneaten ≤1 time.

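### The efficacy analysis is written for parallel groups and leaves the baseline for blocks 2 and 3 of the cross-over unsettled, so some estimates can mislead, depending on baseline and outcome

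*Protocol article*

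**What the plan says.** **Design.** The Abstract has participants "crossing-over at the end of weeks 4 and 8, so that all participants experience all three study arms". Study design gives 12 weeks in total and 4 weeks per arm.

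**Measurement.** Under Efficacy, secondary outcomes "will be assessed at the start (baseline) and at the end of each 4-week block". Table 1 places these visits at weeks 0, 4, 8 and 12. Dietary recall is the exception: week 0, then the third week of each arm (weeks 3, 7 and 11).

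**Analysis.** Data analyses names t-tests, Mann–Whitney and chi-squared tests, and describes the comparison as "comparing the baseline scores for all participants randomised to one arm with end-point scores (at week 4) of all participants for that arm", done likewise for the other two arms. It then extends this to an analysis of variance across arms. The quoted clause is attached to the sentence on categorical variables. The next sentence treats it as the within-intervention analysis of the same outcomes, so it reads as a general rule. The adjustments to be considered are gender, age, comorbidities and BMI.

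**Context.** "All participants will receive 15 min in-person general nutrition and food safety education by a nutritionist at baseline". The control is a weekly AUD 100 voucher, chosen to keep monetary value similar across arms so that food security is not influenced. Meal kits are described as "supporting the development of basic cooking skills with step-by-step guides".

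**The concern.** The rule is phrased as if each participant were randomised to one arm and finished at week 4. In this trial everyone takes all three arms, and week 4 ends an arm only in block 1. For blocks 2 and 3 the rule can be read with week 0 or with the block-start visit as baseline, and the Efficacy wording does not decide between them. With no washout, the block-start value is the end value of the preceding arm. For diet no block-start value exists.

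Preliminary efficacy is a stated aim, and the Discussion says the trial is meant to inform later randomised trials. If the baseline does not suit the outcome, control can appear to change when it did nothing, and the difference between arms can come out too large or too small.

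**Working it through.** **Inputs from the article.** Three blocks of 4 weeks in 12 weeks: 12 - 3 × 4 = 0 weeks for washout. Eighteen participants. Visits as above.

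**Assumptions, because the article gives no figures.** The six orders are equally frequent (18/6 = 3 each). Effects are tP, tK and tC per block, with sum S, and the pre-study level is 0. At first there is no carry-over and no time trend.

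**1. Outcome that reverts within a block (SF-36 as the example).** The end-of-block value is the current arm's effect.
- Block-start baseline: arm X comes first in 2 of 6 orders (start value 0) and follows each other arm in 2 of 6. The mean start value is (S - tX)/3, so the mean change is tX - (S - tX)/3, and any contrast is 4/3 of the truth. With effects d, d, 0: meals d - d/3 = 0.67d; control 0 - 2d/3 = -0.67d; contrast 1.33d.
- Week-0 baseline: changes d, d, 0; contrast d.

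**2. Outcome that accumulates (weight, assumed -1 kg per meal block, control 0).**
- Block-start baseline: changes -1, -1, 0; contrast -1 kg, which is correct.
- Week-0 baseline: each other arm precedes X in half the orders, so the mean change is tX + (S - tX)/2. Meals: -1 - 0.5 = -1.5 kg. Control: 0 - 1 = -1.0 kg. Contrast -0.5 kg, half the truth.

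| Contrast, meal vs control (true = 1) | Block-start baseline | Week-0 baseline |
|---|---|---|
| Reverting outcome | 1.33 | 1.00 |
| Accumulating outcome | 1.00 | 0.50 |

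**3. Week 4 taken literally.** Only block 1 is used: 18 of 54 participant-blocks, or 18/3 = 6 per arm if evenly allocated. The baseline is untreated and the contrast unbiased, but two thirds of the data are unused.

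**4. Carry-over and trend, reverting outcome.** If a fraction L of the preceding arm's effect persists for one block, the week-0 contrast is d(1 - L/3): 0.92d at L = 0.25 and 0.83d at L = 0.5. The block-start contrast is d(4/3 - L/6): 1.29d and 1.25d. A drift of 0.1 SD per block shifts every week-0 within-arm change by (0.1 + 0.2 + 0.3)/3 = 0.2 SD, and cancels from the contrast when orders are balanced. An effect of the baseline education common to all behaves in the same way.

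**5. False significance on control.** Simulation: n = 18, 3 per order, 3000 runs, d = 0.5 SD, no carry-over or trend, two-sided 5%, block-start change. A paired t-test on control rejects in 50% of trials at an assumed within-person correlation of 0.8, and in 96% at 0.95. An unpaired t-test rejects in 2.7% and 0.4%. The article does not say which is meant. The biased estimate (about -0.33 SD) is the same either way.

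**The case against.** A reader might infer that every reading of the rule fails and that the analysis necessarily yields a false control change and distorted contrasts. The documents do not support that: two of the four combinations in the table, and the block-1 reading, give the right contrast.

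Diet cannot illustrate the 1.33 inflation. It has no start-of-block recall, so week 0 is the only baseline available for blocks 2 and 3, and for a reverting outcome that gives an unbiased contrast without carry-over and with balanced orders. Food insecurity is a poor example too: the voucher was chosen to equalise value across arms, so a zero control effect sits badly with the design, and some change on voucher may be real. The education does not bias arm contrasts in balanced orders. That cooking skills persist into the next block is plausible, but the article says only that kits support their development.

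Analysis of variance does not exclude a repeated-measures model with period, and model terms may be left to an unseen analysis plan. That stands, so the absence of a period term is not itself the finding. What remains is what the article does state: a pre-post comparison within each arm, with a week-4 end-point that fits only block 1 and no settled baseline afterwards.

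The outcomes are labelled exploratory, and Limitations concedes that power is inadequate for efficacy. This lowers the severity. It does not answer the point, because low power concerns imprecision, not bias.

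**Conclusion.** The point holds in a conditional form and should be fixed before analysis. A parallel-group pre-post rule is applied to a cross-over without washout, with the baseline for blocks 2 and 3 left open. Under balanced orders and the assumed effects, the contrast can run from half the true value (accumulating outcome, week 0) to one third too large (reverting outcome, block start). No single baseline suits both kinds of outcome. Even where the contrast is right, a within-arm change from week 0 mixes the arm's effect with time trend and the shared education, so it should not be read as efficacy.

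It would be wrong to conclude that the trial's main results are compromised. The Table 2 feasibility and acceptability criteria use no baseline and are unaffected. Nor does the article say that these effect estimates will set the size of the next trial.

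**What to change.** Replace the within-arm testing rule in Data analyses as follows.

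- **Within-arm changes:** report descriptively, with the baseline named, and not as evidence of efficacy.
- **Diet, HFIAS, SF-36, blood pressure, heart rate:** compare end-of-block values (diet: the week-3-of-arm recall) between arms within participant, with arm and period as fixed effects and participant as a random effect. With balanced orders and no carry-over this recovers the true contrast. In the simulation at correlation 0.8 its SD was about 0.15, against 0.24 for block-start changes.
- **Weight, BMI, waist:** analyse change over the same block with arm and period, stating the assumption of no rebound after a meal block. Show the end-of-block comparison as a sensitivity analysis. Under pure accumulation the two give 1.00 and 0.50 of the true contrast; under full reversion, 1.33 and 1.00. At these two extremes they bracket it.
- **Cooking confidence:** show block-1 results and a sensitivity model with a term for the previous arm.
- **Carry-over:** acknowledge that it cannot be fully removed without washout.

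The cost is wording, two model forms instead of one, and slightly more analysis work. All values needed are already scheduled in Table 1.

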a Delivery of the two interventions and adherence to the instructions of both intervention options will not be completed for the control arm.

b The acceptability survey will not be completed for the control arm.

The measures relevant to the primary objective of the trial (i.e. assessment of feasibility and acceptability of two dietary interventions) will be collected through a checklist which participants will be requested to complete daily during the 4 weeks of each intervention arm and weekly for the control arm. To assist participants with completing the dietary checklists, research staff will send SMS reminders to participants and collect the checklists weekly.

This information will be complemented with data obtained from: (a) a semi-structured interview, conducted after participation in both dietary interventions and the control condition (week 12), asking participants about their views and experiences of each intervention; and (b) an acceptability survey, completed in week 3 to align with the 24-h diet recall visit.

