### Limitations

A key limitation of this study is that as a pilot, it is not adequately powered to detect clinical efficacy. In addition, the nature of the intervention prevents blinding of participants and research staff to the diet intervention or control arm. To reduce any potential impact on study outcomes, participants and their treatment teams are informed of their next intervention 1 week before it begins. Although this lack of blinding may have some effect, it is unlikely to significantly influence our primary outcomes. All participants will experience both interventions and the control condition, providing an appropriate scenario to assess the feasibility and acceptability of the intervention, as well as the design needs for a well-powered efficacy study and subsequent implementation studies.

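### The exploratory efficacy analysis rests on within-arm tests and a three-arm ANOVA with no named contrast, so the meal-versus-voucher differences are not what it is set up to report

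*Protocol article*

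**What the plan says.** All places are in the protocol article.

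- **Study design** gives the comparison. The trial is to test feasibility, acceptability and "preliminary efficacy of two dietary interventions compared with an active control condition".
- **Trial visits, assessments and outcome measures** gives the "primary objective of the trial (i.e. assessment of feasibility and acceptability of two dietary interventions").
- **Efficacy** places the rest lower: "Secondary outcome measures (i.e. exploration of the preliminary efficacy of two dietary interventions").
- **Setting and study population** gives the size: "Eighteen eligible participants, aged 18–64 years, will be recruited", each going through all three arms.
- **Data analyses** sets out two layers of testing. The first works by "comparing the baseline scores for all participants randomised to one arm with end-point scores (at week 4) of all participants for that arm", and likewise for the other two arms. The second reads: "This within-intervention analysis will then be extended to compare the same outcomes across the three arms using analysis of variance". Grammatically the first layer is attached to categorical variables, but the second refers back to it as covering the same outcomes, so I read it as applying to all of them.
- The same section promises means and SDs by group. It also promises unstandardised mean differences, but only for baseline symptom severity. For the efficacy outcomes it names no contrast and no interval.
- **Limitations** says that "as a pilot, it is not adequately powered to detect clinical efficacy". It also says that the design lets the team work out what an adequately powered efficacy study would need.

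**The concern.** The question is how each meal arm compares with the voucher. The first layer of analysis answers a different one: whether participants in a given arm changed from baseline. In this trial some change common to all arms is plausible. Everyone receives nutrition and food safety education at baseline, everyone is followed for 12 weeks, and the control is itself a weekly $100 food voucher. A within-arm test credits any such change to whichever arm is being tested. Significance in one arm and not in another could then be read as a difference between arms that was never estimated.

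The second layer is comparative, but its standard test asks only whether any arm differs from any other. It does not by itself give the size of either meal-versus-voucher difference, or how precisely that difference is known. Those are the quantities a pilot should hand to the next trial.

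**Working it through.** The plan states no alpha, SD, correlation or effect size for these outcomes, so there is no figure of its own to reproduce. The inputs are n = 18 (Setting and study population) and these assumptions: two-sided 5% per test, equal SDs, within-person correlation ρ of 0.7 or 0.9 (0.5 added for interval width), and the tests run in paired form, which is the most favourable reading.

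**1. What a within-arm test does when the arms do not differ.** Assume a shift of 0.3 SD from baseline shared by all three arms.

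- SD of the change, in outcome SDs: √(2(1 − ρ)). This is 0.775 at ρ = 0.7 and 0.447 at ρ = 0.9.
- Noncentrality: (0.3 / SD of change) × √18. This is 1.64 at ρ = 0.7 and 2.85 at ρ = 0.9.
- Rejection probability from the noncentral t with 17 df (critical value 2.110): **34%** and **76%**.
- A simulation of 3,000 trials per setting agrees: 34–35% at ρ = 0.7 and 76–78% at ρ = 0.9 in each of the three arms. With no shift, the same tests reject at 5–6%.

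So these rejections come from the shared shift, and they say nothing about meals against voucher.

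The calculation compares each arm with the single week 0 baseline. If the start of each block is used instead, a one-off early shift would enter only for participants who had that arm first, and the figures would be lower. A steady drift would still enter every arm.

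**2. What the group summaries leave open.** In a complete cross-over, subtracting two arm means gives the mean within-person difference, so a point estimate can be recovered. Its precision cannot, because it depends on ρ. The half-width of the 95% interval for one contrast, in outcome SDs, is t(0.975, 32 df) × √(2(1 − ρ)) / √18, with t = 2.037:

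| ρ (assumed) | Half-width (SD) |
|---|---|
| 0.5 | 0.480 |
| 0.7 | 0.372 |
| 0.9 | 0.215 |
| arms treated as independent groups of 18 (51 df) | 0.669 |

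The same arm means and SDs fit any row of this table. Only a reported within-person SD or interval shows which row applies, and the sample size of a later cross-over depends on it.

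**The case against.** The strongest reply is that this is detail. The article is a condensed document, an analysis plan may exist, and an analysis of variance routinely carries contrasts with intervals. That largely stands. A reader might infer that the plan can never give the meal-versus-voucher differences. The text does not support this: it says analysis of variance, not an overall F-test only. What the article does fix is the method it builds on, namely within-arm testing, and that choice is open to comment without seeing an analysis plan.

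Second, efficacy is not the main objective. This stands. Feasibility and acceptability are primary and are judged against the criteria in Table 2, which this point does not touch.

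Third, a reader might go on to a multiplicity charge: 24 secondary outcomes × (3 within-arm tests + 1 ANOVA) = 96 tests, with a 99% chance of at least one false positive. This should not be pressed. The plan states no such count. Depending on how the dietary and physical measures are split, there are 16 to 38 outcomes, hence 64 to 152 tests. The 99% assumes independence, which does not hold, and leaving exploratory pilot outcomes unadjusted is not an error.

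Fourth, it is tempting to argue that the F-test has less power than planned contrasts. With assumed meal effects of 0.8 and 0.4 within-person SD, F has 52.6% power against 64.5% for the larger contrast. Bonferroni for two contrasts brings the latter to 52.8%. If both effects are 0.8, F has 65.7% against 64.5% per contrast. Power does not decide the matter.

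**Conclusion.** The concern holds in a limited form. The Data analyses section builds the exploratory efficacy analysis on within-arm change and names no contrast for the ANOVA that follows, so the comparison set in Study design is not the one the analysis is arranged to report. The risk is misreading: with no arm difference and a shared 0.3 SD shift, about one within-arm test in three (ρ = 0.7) or three in four (ρ = 0.9) would be significant. The shift, the correlations and the 5% level are assumptions, since the article gives none of them.

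Severity is minor. The outcomes are secondary and exploratory, the article already says that it lacks power for efficacy, and the primary criteria are unaffected. A reader might also infer that all p-values should be removed from the secondary outcomes. That is a matter of preference, and nothing in the article makes exploratory p-values wrong.

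**What to change.** In Data analyses, replace the within-arm tests and the unspecified ANOVA for the secondary outcomes with two within-person contrasts per outcome: pre-prepared meals minus voucher, and meal kit minus voucher. Report each with its 95% confidence interval and within-person SD. If the ANOVA is kept, say that it is the repeated-measures model from which these two contrasts are taken. Present change from baseline within each arm descriptively, without significance tests, and label any remaining p-values exploratory.

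This changes wording only: no new data, visits or participants. The cost is that the sponsor gives up reporting statistically significant change within an arm.

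### Table 2 implies 24 meal-kit servings where the text promises one meal a day for 4 weeks (28), and the 80%-of-days eating criterion does not fix its denominator

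*Protocol article*

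**What the plan says.** On supply, the Meal kits section under Intervention procedures gives one rule for both dietary arms: "For each dietary intervention phase, participants will receive one meal daily, delivered weekly, for 4 weeks". It adds that "A similar amount of kilojoules (kJ) will be provided per week by the meals", with each meal between 2600 and 2900 kJ.

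On the success criteria, Table 2 (Data analyses) lists three meal-adherence items for the kit arm:

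- The first is a minimum for following the instructions: "Recipe followed at least 50% of time (six of 12 recipes".
- The second concerns portioning, and requires every recipe that is attempted to be divided into two servings.
- The third is the eating threshold: "Half or more of the meal serving was eaten ≥80% of the days".

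The pre-prepared arm has one item, with almost the same wording as the third: "Half or more of the meal was eaten ≥80% of the days".

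On data collection, the section on trial visits and assessments describes a checklist that "participants will be requested to complete daily during the 4 weeks of each intervention arm and weekly for the control arm". The kit checklist item is worded per day: "Did you eat the prescribed portion of the meal kit meal today".

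**The concern.** Twelve recipes split in two do not make one meal a day for 4 weeks, and the article does not account for the four missing servings. This would be a small slip if the count did not feed a primary-outcome threshold. It does, because the eating criterion is a percentage of days and is applied in the same terms to both meal arms. If one arm has a serving for every day and the other does not, the same percentage of days demands more of the second arm. The same eating behaviour could then pass with pre-prepared meals and fail with kits because of the denominator alone. These criteria are meant to inform the design of later trials.

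**Working it through.** **Inputs.** Meal kits section: one meal daily, 4 weeks, 2600 to 2900 kJ per meal. Table 2: 12 recipes, two servings per recipe, threshold 80% of days, recipe threshold 50%. Trial visits section: daily checklists for 4 weeks.

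**The plan's own figure.** 6/12 = 50%, so the recipe threshold is correct as a percentage of 12.

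**Servings.**
- By the supply statement: 7 × 4 = 28.
- By Table 2: 12 × 2 = 24, or 24/4 = 6 a week.
- Gap: 28 − 24 = 4 servings (4/28 = 14.3%).
- Recipes needed for 28 servings: 28/2 = 14.

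**Servings needed for the eating criterion.** The number needed is the smallest whole number at or above 0.80 × the denominator.
- 28 days: 0.80 × 28 = 22.4, so 23 (22/28 = 78.6% fails; 23/28 = 82.1% passes).
- 24 serving days: 0.80 × 24 = 19.2, so 20 (20/24 = 83.3%).

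| Kit servings supplied | Denominator for kits | Kits need | Pre-prepared need |
|---|---|---|---|
| 24 | 28 checklist days | 23 of 24 (95.8%) | 23 of 28 (82.1%) |
| 24 | 24 serving days | 20 of 24 (83.3%) | 23 of 28 (82.1%) |
| 28 | 28 days | 23 of 28 (82.1%) | 23 of 28 (82.1%) |

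**Illustrative pass probabilities.** Assume each supplied serving is at least half eaten with probability p, independently. The protocol gives no value for p, so a range is shown. P(X ≥ k) = Σ C(n, j) p^j (1 − p)^(n − j), summed over j from k to n. For 23 of 24 at p = 0.90 this is 24 × 0.9^23 × 0.1 + 0.9^24 = 0.292.

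| p | Pre-prepared, 23 of 28 | Kit, 23 of 24 | Kit, 20 of 24 |
|---|---|---|---|
| 0.85 | 0.765 | 0.106 | 0.713 |
| 0.90 | 0.945 | 0.292 | 0.915 |
| 0.95 | 0.998 | 0.661 | 0.994 |

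**Recipe item against eating item, at one serving per day.**
- 6 recipes prepared: 12 servings, 12/28 = 42.9% or 12/24 = 50%. Fails on both denominators.
- 10 recipes: 20 servings, 71.4% of 28 (fails) or 83.3% of 24 (passes).
- 11 recipes: 22 servings, 78.6% of 28 (fails).
- 12 recipes: 24 servings, 85.7% of 28 (passes).

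So a kit participant must prepare all 12 recipes on the 28-day reading and at least 10 on the 24-day reading.

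**Weekly energy, only if kits supply 6 meals a week and the other arm 7.** 6 × 2600 to 6 × 2900 = 15,600 to 17,400 kJ; 7 × 2600 to 7 × 2900 = 18,200 to 20,300 kJ. The ranges do not overlap.

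**The case against.** The strongest reply is that the asymmetry between arms depends on how the text is read. It needs three things together: kits supplying 24 servings, pre-prepared meals supplying 28, and kits being scored over 28 days. The supply statement covers both dietary phases. If it governs, kits also supply 28 and both arms need 23 of 28. Nor does Table 2 say which days count. The kit item asks about that day's kit meal, so it could be scored only on days with a serving, and the checklist itself is in a supplementary file not shown here. This stands. The 28-day denominator is the natural reading of one meal daily with daily checklists, but it is not stated.

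Three stronger readings are tempting, and the document does not support them:

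- *The recipe item and the eating item cannot both be met.* They can. The 50% figure is a minimum, so a participant who follows all 12 recipes and eats 23 servings meets both, even over 28 days. Following a recipe is also distinct from attempting one, so six recipes followed and six prepared another way could meet both. All that remains is that the recipe minimum lies well below what the eating item demands.
- *The trial would declare kits infeasible, or rank them lower, on this item.* No such rule is given. It is one of several kit criteria, and the ranking in Table 2 is the participants' own preference.
- *The energy statement is a separate error.* It fails only if kits supply fewer meals than the other arm, so it follows from the same mismatch.

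None of this removes the disagreement between 24 and 28. Both counts come from the article, and further detail elsewhere cannot make 12 × 2 equal 28.

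**Conclusion.** The contradiction holds without any assumption about the denominator: the supply statement implies 28 servings, Table 2 implies 24, and one of them must change. The document does not show which.

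The effect on the eating criterion is conditional. With 24 kit servings scored over 28 days, kits must reach 95.8% of servings supplied against 82.1% for pre-prepared meals, and at an assumed p of 0.90 the pass probabilities are about 29% and 94%. With 24 serving days the contrast shrinks to about 91% against 94%. With 28 kit servings it vanishes, and only the recipe count is wrong. If kits do supply 24 servings, two defensible readings of one predetermined criterion move the kit pass probability from about 29% to about 91% at p = 0.90, which is reason enough to fix the denominator in writing. These probabilities assume independence between servings and are illustrations, not predictions.

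**What to change.** 1. Reconcile the number of kit servings between the Meal kits section and Table 2. If the count changes, correct the recipe threshold to match; for example, 50% of 14 recipes would be 7, since 6/14 = 42.9%.
2. In both meal arms, define adherence as servings at least half eaten divided by servings supplied, with the same 80% threshold. This gives 20 of 24 or 23 of 28, according to the reconciled count.
3. State that the 50% recipe item measures instruction-following only, so that it is not read as a sufficient level of preparation for the eating item.
4. Only if kit servings stay below the pre-prepared count, correct the statement of similar weekly energy and report the energy supplied per arm.

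The cost is an edit to Table 2, possibly a sentence in the Meal kits section, and a check of the order plan, which should already show the number of meals supplied. No new data collection is needed.
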